Driving simulators have been demonstrated to be accurate proxies for real-world driving and are an effective way to evaluate the impairing effects of various substances under safe conditions (Veldstra et al., 2015; Helland et al., 2016). Collectively, prior studies have revealed that alcohol and/or high Δ9-THC cannabis can impact various facets of driving. Alcohol has reliably been shown to adversely impact lane weaving (or standard deviation of lateral position, SDLP), performance on driving tasks of divided and sustained attention, reaction time, and various other driving performance metrics (e.g., centerline and road-edge crossings). Moreover, alcohol tends to lead to more reckless driving, as evidenced by increasing speed (or more variable speed: standard deviation of speed, SDSP), shortening following distance to lead vehicles, or running red lights or stop signs, all of which may increase the likelihood of accidents. Impairment on these driving performance outcomes is typically observed at a BAC of 0.05% (or lower) and generally increases in a dose-orderly fashion. High Δ9-THC cannabis also negatively impacts simulated driving performance (Martin et al., 2013; Jongen et al., 2016; Irwin et al., 2017; Van Dijken et al., 2020). As with alcohol, high Δ9-THC cannabis reliably increases lane weaving (i.e., SDLP); SDLP has consistently been the most sensitive driving outcome measure following acute high Δ9-THC cannabis exposure (as with alcohol, high Δ9-THC cannabis reliably increases SDLP; Arkell et al., 2020; Marcotte et al., 2022). Likwise, SDLP and other measures of lateral control are particularly impacted by high Δ9-THC cannabis during controlled driving tasks that are more cognitively demanding than regular driving (e.g., divided attention or car following tasks; McCartney et al., 2021; Marcotte et al., 2022; Simmons et al., 2022; Thawer et al., 2022). Unlike alcohol, high Δ9-THC cannabis tends to lead to reduced driving speed (McCartney et al., 2021; Simmons et al., 2022; Thawer et al., 2022). Other driving outcomes are also negatively impacted by high Δ9-THC cannabis (e.g., reaction time, ancillary outcomes on divided attention or car following tasks), albeit in a less consistent fashion than SDLP and speed (McCartney et al., 2021). These inconsistent results are likely due to differences in Δ9-THC doses administered and dosing procedures (e.g., *ad libitum* vs. fixed dosing), and the types of simulations/scenarios used across studies. Though relatively few studies have administered cannabis and alcohol concurrently, co-use of alcohol and high Δ9-THC cannabis has been found to produce additive or synergetic driving impairment, again as evidenced most clearly by measures of lateral control (e.g., SDLP; Hartman et al., 2015; Simmons et al., 2022).

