**FIGURE 3 F3:**
[figure not shown]
The car-following task occurs behind a white SUV over a duration of 5 min. The primary outcomes for this scenario are standard deviation of lateral position (SDLP), the car’s modulus, and the coherence to the task.

The primary outcome measures for this task include SDLP (a composite measure of lane weaving, swerving, and over-correcting), car-following modulus, response delay, and coherence. The modulus variable indicates how well the participant’s speed matches the lead vehicle’s speed; a value of 1 represents a perfect match, values greater than 1 indicate the participant generally drove faster than the lead vehicle, which indicates tailgating behavior, and values under 1 indicate the participant tended to drive slower than the lead vehicle. Car-following delay represents the amount of time it takes for the participant to respond to speed changes by the lead vehicle. Car-following coherence demonstrates how well the participant’s overall data matches that of the lead vehicle; coherence is expressed as a correlation from 0–1 (0 = no correlation between participant’s and lead vehicle’s data; 1 = perfect correlation between the two vehicles’ data).

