**FIGURE 6 F6:**
[figure not shown]
Stop light interactions for **(A,B)** amber dilemmas and **(C,D)** stop light reaction test that occur throughout the drive in rural and urban environments. During amber dilemmas, participants will approach a green light **(A)** that will change to yellow **(B)** 3.5 s from the intersection. During the stop light reaction test, participants will approach a green light that will change to yellow **(C)** 5.5 s from the intersection and then to red **(D)** 3.5 s after the yellow transition. The primary outcomes for these events are response to the traffic signal (i.e., stop or go through the light), reaction time to the signal light, and if participants stop, their response time to a green signal light.

The second stoplight scenario, the stoplight reaction test, is similar to the amber dilemma in that a traffic light turns yellow as a driver approaches. However, in this scenario, the light turns yellow much earlier (at a headway time of 5.5 s) and the correct response is for the participant to stop (Figures 6C,D). If they proceed through the light, they receive a ticket. Each drive contains one stoplight reaction test. The primary outcome measures for amber light dilemmas and stoplight reaction tests are reaction time to respond to the yellow light change (either gas or brake response) and whether the participant proceeded through or stopped at the light. For the stoplight reaction test, an additional outcome measure is reaction time to begin driving again in response to a green light (assuming the participant did not run the yellow light).

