For the FTN, participants are asked to stand with their feet together and arms at their side, with both index fingers pointed at the ground and their eyes closed and head tilted back. They are then instructed to touch the tip of their index finger to their nose in a specified order. Possible cues of impairment include: failure to follow the instructed order of nose presses and number of failed attempts at touching the tip of their finger to their nose.

The total number of clues/cues of impairment detected will be summed to produce an overall score for each task (our primary outcomes), with higher scores indicating greater impairment; another outcome is the cumulative number of clues/cues of impairment across all tests. Participants are video recorded while performing the field sobriety tests to allow for a second person to score the tests at a later time; agreement between these two coders will be calculated and individual discrepancies between coders will be resolved by a third coder. Eye-related tests are filmed *via* a GoPro mounted on the administrator’s forehead. To further ensure proper technique is followed by task administrators and that clues/cues of impairment were scored correctly, the aforementioned retired DRE who helped train the research staff will score a subset of the recorded tests (approximately 25%, chosen at random). All SFSTs will be given at baseline and at various timepoints after drug administration (up to 7.5 h post-dosing). Each of these tests will be administered immediately after driving.

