### 2.10 Subjective drug effects

A modified 25-item Drug Effect Questionnaire (DEQ; Spindle et al., 2018; Spindle et al., 2021) will be administered that includes items assessing: positive (e.g. “like drug” and “pleasant drug effect”) and negative subjective drug effects (e.g. “unpleasant drug effect” and “anxious/nervous”), behavioral/mood states related to acute high Δ9-THC cannabis exposure (e.g. “high”, “paranoid”, and “hungry/have munchies”), and participants’ perceived level of impairment (e.g. “trouble with memory”, “difficulty with routine tasks”, “confidence in driving ability”). Each item will be presented individually on a 100 mm visual analog scale (VAS) with a horizontal line anchored from 0 (“not at all”) on the left to 100 (“extremely”) on the right. The one exception is the question, “Would you drive in your current state,” which requires a yes or no response.

The Subjective High Assessment Scale (SHAS) (Martin et al., 1993) and the Biphasic Alcohol Effects Scale (BAES) (Schuckit, 1980) will be administered to assess alcohol-specific subjective effects. For the SHAS, participants rate alcohol effects on a 100 mm VAS (0 or “not at all” to 100 or “extremely”). Example items include: muddled/confused, slurred speech, dizzy, drunk, distorted sense of time, and difficulty concentrating. Items are summed to produce an overall score (the primary SHAS outcome). The BAES measures stimulant (e.g., energized, excited, stimulated) and sedative (e.g., inactive, sedated, sluggish) effects of alcohol with 14 items. Participants rate each item on a scale from 0 (“not at all”) to 10 (“extremely”). Overall stimulant and sedative scores are calculated from the individual items (two primary BAES outcomes). These questionnaires, along with the DEQ, will be given at baseline and at various timepoints after drug administration (see Figure 1). These questionnaires will be administered immediately before driving.

After each drive, participants will answer two questions to assess their perceived driving performance: “how much did the study drugs affect your driving?” (0 [not at all] to 100 [extremely]) and “how well did you drive?” (0 [not well at all] to 100 [extremely well]).

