### 2.14 Data presentation and statistical analysis plan

Power analyses for each primary outcome were conducted in R, using the SIMR package (Green and Macleod, 2016), which estimates power for linear mixed models by fitting a regression model multiple times under different scenarios, or simulations (100 simulations were performed for each power calculation). Effect sizes (Cohen’s d) and data (means and SDs) were obtained from prior alcohol/cannabis co-use studies (Hartman et al., 2016a) and/or prior studies conducted in our laboratory (Spindle et al., 2018; Spindle et al., 2021) that administered the proposed doses of oral/vaporized cannabis or alcohol alone. Overall, all power analyses revealed that 32 participants (16 men/16 women) in Part 1 and Part 2 would provide sufficient power (≥ 0.80 power for all 100 simulations) to test the study hypotheses stated.

For each outcome, descriptive statistics (means and standard deviations) will be generated. Linear mixed models will be used to test for differences across experimental conditions. Hypothesis tests will be two-sided, and significance will be set at *p* < 0.05. Factors entered into these models will include: Time (number of levels will differ depending on outcome variable), Alcohol Dose (0%, 0.05%, and 0.08%), Cannabis Dose (0, 10, and 25 mg Δ9-THC), and Sex (male or female). Time, alcohol dose, and cannabis dose will be within-subject factors (i.e., repeated measures); sex will be a between-subject factor. Maximum concentration (C_max_) and area under the curve (AUC) for Δ9-THC and Δ9-THC metabolites (11-OH-Δ9-THC; Δ9-THC-COOH) will be entered as covariates. Holm-Bonferroni corrections will be used to control for multiple comparisons. Data will be inspected for normality (skewness, kurtosis, outliers) and, where necessary, data transformations will be applied. Missing data is expected to be rare, as tasks and instruments are computerized, and field sobriety tasks will be video recorded. Additionally, if a participant presents elevated concentrations of Δ9-THC or Δ9-THC metabolites at baseline, and these values do not increase following active drug administration, this participant will be excluded from analysis.

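### Linear mixed models, transformation and mean peak change are the only methods named, and they do not suit the yes/no and sparse-count outcomes; signed modulus alone can miss two-sided deviations

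*Protocol article*

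**What the plan says.** Section 2.14 opens its analysis description with "For each outcome, descriptive statistics (means and standard deviations) will be generated" and continues with "Linear mixed models will be used to test for differences across experimental conditions". Time, alcohol dose, cannabis dose and sex are the factors. Its answer to non-normality is: "Data will be inspected for normality (skewness, kurtosis, outliers) and, where necessary, data transformations will be applied". The planned comparisons in the same section are of mean peak change from baseline, again for every outcome. No binomial, ordinal or count model is named.

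The outcomes to which this applies include:

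- **Stop lights (2.7.7).** One primary outcome is "whether the participant proceeded through or stopped at the light". Each drive has two amber dilemmas and one stoplight reaction test.
- **Field sobriety tests (2.9).** Each clue is scored 0 or 1. "The total number of clues/cues of impairment detected will be summed to produce an overall score for each task (our primary outcomes"). The stated ranges are 0 to 4 for the one-leg stand and the Romberg test, 0 to 6 for horizontal gaze nystagmus and 0 to 8 for walk-and-turn. Lack of convergence appears to have a single cue, hence a 0/1 score.
- **Willingness to drive (2.10).** A questionnaire item "which requires a yes or no response". It is not labelled primary.
- **Collisions.** These are a count in 2.7.1. The Figure 5 legend lists them as primary, although the text of 2.7.6 names only reaction time and time-to-collision.
- **Car-following modulus (2.7.3).** This is primary, and 1 is a perfect match. On one side, "values greater than 1 indicate the participant generally drove faster than the lead vehicle, which indicates tailgating behavior"; on the other, the participant drove slower.

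**The concern.** There are three separate difficulties.

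1. **Variance.** The variance of a 0/1 outcome is p(1 − p), so it moves with the event rate. A linear mixed model with one residual variance gives every condition the same precision. The design runs from double placebo to 25 mg with alcohol, and to the 0.08% positive control, so rates could differ widely. Transformation cannot help, because a two-valued variable remains two-valued.
2. **Peak change.** For a yes/no outcome, the peak over four post-dose drives is whether the event ever happened. That proportion moves towards its ceiling and leaves little room for a drug effect to show.
3. **Modulus.** Performance worsens on both sides of 1. The Introduction says alcohol tends to increase speed, and then: "Unlike alcohol, high Δ9-THC cannabis tends to lead to reduced driving speed". If participants in the same condition deviate in opposite directions, the signed mean can sit at 1 while individuals follow the lead vehicle badly.

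At stake are misstated intervals and p-values for some primary outcomes, and co-use effects that go unseen.

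**Working it through.** **Inputs from the protocol article.** There are 32 participants per part and seven conditions (2.1, 2.14), two-sided 0.05 (2.14), and four post-dose drives (2.6). The article prints no event rate, standard deviation or effect size. Its stated power of at least 0.80 therefore cannot be reproduced, and this point does not bear on it. All rates below are assumptions.

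**1. Standard errors on 0/1 data.** Assume rates of 3, 5, 10, 10, 20, 30 and 30% in the seven conditions, with independent responses.

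- Variances p(1 − p): 0.0291, 0.0475, 0.09, 0.09, 0.16, 0.21, 0.21. Mean = 0.8366/7 = 0.1195.
- Model standard error of any two-condition difference: √(2 × 0.1195/32) = 0.0864.
- True standard error, two conditions at 10%: √(2 × 0.09/32) = 0.0750. Ratio 0.0864/0.0750 = 1.15.
- True standard error, two conditions at 30%: √(2 × 0.21/32) = 0.1146. Ratio 0.0864/0.1146 = 0.75.
- Normal-approximation type I error, 2Φ(−1.96 × ratio): 2.4% and 13.9%.

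A simulation (20,000 replicates, random-intercept linear model with pooled residual variance) agrees. I held the marginal rates fixed and varied the between-person SD on the logit scale:

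| Between-person SD | 10% pair | 30% pair |
|---|---|---|
| 0 | 2.1% | 13.9% |
| 1 | 2.2% | 12.7% |
| 1.5 | 2.3% | 11.7% |
| 2 | 2.0% | 10.6% |

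A paired t-test on the same data stayed between 4.0% and 5.1%.

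Other assumed patterns (10,000 replicates, between-person SD 1):

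| Rates | Model SE / true SE | Type I error |
|---|---|---|
| All 50% | 1.00 | 4.9% |
| All 5% | 0.99 | 4.7% |
| 10% to 35% | 1.00 | 4.5% |
| Compared pair 3%, most others 30% to 50% | 1.83 | 0.1% |
| Compared pair 50%, others 3% | 0.68 | 18.5% |

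The problem therefore needs strongly different rates. With similar rates the linear model is close to right.

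**2. Transformation of counts.** Skewness of a Poisson count, raw and then after log(1 + y) and square root:

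- mean 0.1: 3.2 raw; 2.9 and 2.8 transformed
- mean 0.3: 1.8 raw; 1.3 and 1.2 transformed
- mean 1: 1.0 raw; 0.1 and −0.1 transformed

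Transformation fails for very sparse counts and works reasonably at a mean of about 1.

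**3. Peak over four drives.** Take one light, an assumed go rate of 50% per drive, and independent drives.

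- No drug effect: P(any go) = 1 − 0.5⁴ = 93.75%.
- Go rate raised to 70% on one drive: 1 − 0.5³ × 0.3 = 96.25%.
- Baseline has the same expectation in both conditions, so the difference in peak change is 96.25 − 93.75 = 2.5 points. The difference on that drive is 20 points.

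**4. Modulus.** If 16 participants sit at 1.2 and 16 at 0.8, the mean signed deviation is (16 × 0.2 − 16 × 0.2)/32 = 0.00, while the mean distance from 1 is 0.20. With an assumed noise SD of 0.1 and shifts of ±0.1, a paired test rejects in 1.7% of simulations on the signed change and 53% on the change in distance from 1.

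**The case against.** The strongest defence is that this is a condensed article. The sentence on linear mixed models does not itself say every outcome, and a fuller plan may name other models. That is fair as far as it goes. However, the Introduction says the article sets out the analysis plan, the neighbouring sentences do say each outcome, and the one remedy offered cannot work for binary data. The text states a method; it is not merely silent.

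Other objections stand, and they rule out stronger readings that a reader might infer:

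- **That error bars are wrong throughout.** They are not. Type I error is near 5% when rates are similar, and the article gives no rates.
- **That peak change creates false drug effects.** With a constant rate of 5, 10 or 20% per drive, expected peak change with no drug effect is 1 − (1 − p)⁴ − p, which is +14, +24 or +39 points. But the plan compares conditions and does not test change against zero, so the offset cancels between conditions with equal rates. Loss of signal is the real defect.
- **That transformation is useless for all counts.** It helps the less sparse ones, which may include clue totals running to 6 or 8.
- **That co-use will look unimpaired on modulus.** The Introduction gives average directions by drug, for driving speed in general. If the two drugs offset within a person, that person's modulus is near 1 and distance from 1 shows nothing either. Cancellation needs participants in one condition to deviate in opposite directions, and the article nowhere says they do. The signed value also has its own meaning in 2.7.3, and lateral position, delay and coherence are primary for the same task.

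The alternative models have a weakness too. At a 3% rate, the chance that a condition has no events among 32 participants is 0.97³² = 38%, so an ordinary logistic mixed model may not be estimable.

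**Conclusion.** The point holds in limited form and is worth correcting. As printed, section 2.14 applies linear models, transformation and mean peak change to outcomes they do not fit. The clearest case is stop or go at the lights. Lack of convergence (0/1 by inference), the yes/no driving item (not primary) and sparse counts such as collisions follow.

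Under assumed rates of 3% to 30% with one pooled variance, type I error is about 2% for a pair of conditions at 10% and about 12% to 14% for a pair at 30%. The second figure falls to 10.6% if participants differ very strongly. Under similar rates there is no material error. The peak summary can reduce a 20-point effect on one drive to 2.5 points, assuming a 50% go rate and independent drives.

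For modulus, the signed mean can miss deviations that go both ways between participants. This is a possibility, not something the article predicts. Nothing here questions the linear models for continuous outcomes or the sample size of 32.

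**What to change.** Amend the analysis wording in 2.14:

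- Keep linear mixed models for continuous outcomes.
- Use logistic mixed models for stop or go, lack of convergence and the yes/no driving item.
- Use proportional-odds or beta-binomial mixed models for short clue counts.
- Use Poisson or negative binomial mixed models for collisions and similar event counts.
- Analyse these outcomes per time point, not as peak change.
- Name a penalised or exact paired fallback for any condition with no events.
- For modulus, keep the signed test and add distance from 1, for example |log modulus|. State how peak is defined for a measure that worsens in both directions.

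The cost is plan wording and standard software, with no change to conduct or data collection. The drawbacks are that results for these outcomes are on odds or rate ratio scales, and that sparse cells may need penalised estimation.

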
The primary aim of this two-part study is to characterize subjective, cognitive and psychomotor, and driving impairment from oral and vaporized high Δ9-THC cannabis, when administered alone and in combination with alcohol. A secondary aim is to explore possible pharmacokinetic interactions between alcohol and oral/vaporized cannabis. A key aspect of this protocol was the development of custom simulated driving scenarios designed to test important aspects of driving performance that are known to be impacted by alcohol and cannabis exposure. By incorporating different tasks and scenarios that have been independently found to be sensitive to alcohol and cannabis effects, this custom simulation can provide a holistic view of how these substances impact driving performance when taken alone and together. To promote greater standardization and future cross-study comparisons among simulated driving studies, we describe the characteristics of the custom drive scenarios and provide a copy of the simulated drives along with an R script to extract and organize the data (available for download at https://github.com/[name]/STISIM_impaired_driving). Below we also describe the study procedures and specific outcome measures, detail our statistical analysis plan, and conclude by commenting on the implications that this research can have for public safety as well as policy and regulatory decisions for alcohol and cannabis.

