## 2 Methods

### 2.1 Study design overview

The study is a two-part, randomized, double-blind, placebo-controlled, crossover study examining the acute effects of oral high Δ9-THC cannabis (Part 1) or vaporized high Δ9-THC cannabis (Part 2) and alcohol, alone and in combination, on various pharmacodynamic (e.g., cognitive/psychomotor/driving performance, subjective drug effects) and pharmacokinetic outcomes. All study participants will complete seven separate outpatient sessions where they will consume a cannabis-infused brownie (containing 0, 10, or 25 mg Δ9-THC) or inhale vaporized cannabis (containing 0, 10, or 25 mg Δ9-THC) and a drink that contains placebo or alcohol (alcohol-containing drinks will be calculated to produce a BAC of 0.05%). Placebo drinks contain 1 ml of alcohol, which is placed on top of the beverage immediately prior to dosing and contain an alcohol-soaked hair tie as part of blinding procedures (to mask smell and taste sensory cues). There will also be a positive control session where participants will administer placebo cannabis with an alcohol drink calculated to produce a BAC of 0.08% (selected due to its common use as a *per se* threshold for law enforcement to enforce driving under the influence (DUI) laws). Each session will be conducted at the Johns Hopkins Behavioral Pharmacology Research Unit (BPRU), will last approximately 10 h, and will be separated by at least 1 week to allow for sufficient drug washout. Experimental procedures are approved by the Institutional Review Board of Johns Hopkins University School of Medicine (IRB00290015) and will be conducted in accordance with the Declaration of Helsinki. Part 1 is registered with ClinicalTrials.gov (NCT04931095) and the project was funded by the National Institute on Drug Abuse (R01-DA052295 to [name]).

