0	0.05	0	0.05
10	0.05	10	0.05
25	0.05	25	0.05
0	0.08	0	0.08

BAC, 0.08 serves as the study’s positive control in Part 1 and Part 2.

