For Part 1 and Part 2, a priori planned comparisons will be conducted to compare mean peak change-from-baseline scores for each outcome for: (1) alcohol alone (BAC 0.05%) to alcohol with cannabis (BAC 0.05% + 10 mg Δ9-THC and 25 mg Δ9-THC); and 2) cannabis alone (10 mg Δ9-THC and 25 mg Δ9-THC) to cannabis with alcohol (BAC 0.05% + 10 mg Δ9-THC and 25 mg Δ9-THC). Additionally, planned comparisons will compare impairment (e.g., DRUID scores, composite drive scores) between cannabis with alcohol (BAC 0.05% + 10 m g Δ9-THC and 25 mg Δ9-THC) to the positive control condition (alcohol alone: BAC 0.08%). Correlations will be conducted to assess the relations between DRUID and driving performance. Sensitivity and specificity analyses will be conducted to characterize the effectiveness of the DRUID for determining driving impairment. Specifically, we will plot the sensitivity (true positive rate) and specificity (true negative rate) of the DRUID at identifying impaired driving by comparing various DRUID cutoffs to established cutoffs for driving simulator data that are indicative of clinically meaningful impaired driving in real-world settings (e.g., SDLP change-from-placebo ≥ 2.4 cm; Jongen et al., 2016). Sensitivity and specificity will be calculated as follows: sensitivity (100 × [TP/(TP + FN)]) and specificity (100 × [TN/(TN + FP)]).

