This study was designed to maintain a high degree of scientific rigor and experimental control, while also providing ecologically valid and generalizable data. Participants will complete 7 double-blind, double-dummy outpatient sessions where they will administer placebo or active cannabis (10 or 25 mg Δ9-THC) and a placebo drink or alcohol drink calculated to produce a BAC of 0.05%; there is also a positive control session with placebo cannabis and alcohol at a target BAC of 0.08%. The double-dummy design in which participants always receive both an experimental beverage (containing alcohol or placebo) and cannabis (active or placebo) will help control for expectancy effects for both drugs. The within-subject crossover design where participants serve as their own control will greatly reduce variability due to individual differences in drug metabolism, sensitivity, and other factors, and increase statistical power. The cannabis doses were informed based on our prior research (Vandrey et al., 2017; Spindle et al., 2018; Spindle et al., 2021), which showed that 10 mg Δ9-THC elicits discriminable drug effects but little to no impairment while 25 mg Δ9-THC reliably impairs cognitive/psychomotor performance. Thus, these two doses are ideal for testing the sensitivity of the various performance measures in this study. Moreover, these Δ9-THC doses are ecologically valid, as they are common among retail cannabis products sold in dispensaries (Hammond, 2021). Target BACs were selected based on *per se* limits for alcohol in most U.S. states (0.08%) and most of Europe (0.05%). Dosing participants to a 0.05% BAC in alcohol and cannabis co-use conditions will also avoid ceiling effects on study outcomes and mitigate potential untoward drug effects (e.g., emesis) that may be present if higher alcohol doses were given with cannabis. This study design will also reveal whether alcohol (at a BAC below the U.S. legal limit for DUI) and oral/vaporized cannabis have additive or synergistic effects when combined that meet or exceed the effects produced by alcohol alone at a higher BAC (0.08%) that does constitute DUI. Lastly, the proposed timing of cannabis and alcohol administration will ensure that peak cannabis effects (for both oral and vaporized cannabis) coincide with peak alcohol effects, thus capturing the “worst-case scenario” in terms of impairment from alcohol/cannabis co-use for both routes of administration.

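### The planned comparisons leave out the placebo/placebo session and any interaction contrast, and the stated 3 × 3 factors cover only 7 of 9 cells, so the mixed model as specified does not fill the gap

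*Protocol article*

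**What the plan says.** The aim, in the last paragraph of section 1, is broad: "The primary aim of this two-part study is to characterize subjective, cognitive and psychomotor, and driving impairment from oral and vaporized" cannabis, given alone and together with alcohol. Section 3 adds that the design will reveal whether the two drugs "have additive or synergistic effects when combined that meet or exceed the effects produced by alcohol alone at a higher BAC (0.08"%), and its closing paragraph links such a result to a possibly lower legal limit for people who co-use.

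On design, section 2.1 states: "All study participants will complete seven separate outpatient sessions". Table 1 lists them as mg THC/target BAC: 0/0, 10/0, 25/0, 0/0.05, 10/0.05, 25/0.05 and 0/0.08. Its footnote reads: "BAC, 0.08 serves as the study’s positive control in Part 1 and Part 2". The 0.08% drink is given only with placebo cannabis.

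On analysis, section 2.14 gives a linear mixed model with Time and "Alcohol Dose (0%, 0.05%, and 0.08%), Cannabis Dose (0, 10, and 25 mg Δ9-THC), and Sex (male or female"). It names no interaction term. The planned comparisons of mean peak change from baseline are:

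- "alcohol alone (BAC 0.05%) to alcohol with cannabis (BAC 0.05% + 10 mg Δ9-THC and 25 mg Δ9-THC");
- "cannabis alone (10 mg Δ9-THC and 25 mg Δ9-THC) to cannabis with alcohol" at the same doses;
- co-use at each dose "to the positive control condition (alcohol alone: BAC 0.08"%).

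Holm-Bonferroni is the stated multiplicity correction. The only other mention of placebo in the planned analyses is as the reference for an SDLP cutoff in the DRUID sensitivity and specificity analysis.

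**The concern.** Three statements the trial wants to make need contrasts that are not on the list.

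- **Effects alone.** Impairment from 10 mg, 25 mg or 0.05% alcohol by itself has to be judged against the 0/0 session. Change from the same day's baseline is no substitute. The planned outcome is a peak change, and a peak over four post-dose drives (1.5, 3.5, 5.5 and 7.5 h) tends to be positive from noise alone, even under placebo.
- **The positive control.** If an outcome is insensitive, co-use and 0.08% alcohol will look alike. Without 0.08% against placebo, that similarity could be taken for impairment equal to the legal threshold.
- **Additive or synergistic.** These words describe how the joint effect relates to the sum of the single effects. Comparing co-use with each drug separately does not measure that.

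The mixed model would have to carry all three, and its stated factors do not match the sessions run.

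**Working it through.** **Inputs.** The seven conditions come from Table 1; the comparisons, model factors and n = 32 per part come from section 2.14. Section 2.14 reports power of at least 0.80 but gives no effect sizes or SDs, so that figure cannot be reproduced. The argument does not need it.

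**1. What the planned comparisons span.** Write μ(c,a) for the mean at c mg and BAC a. The six contrasts are:

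- μ(10,.05) − μ(0,.05) and μ(25,.05) − μ(0,.05)
- μ(10,.05) − μ(10,0) and μ(25,.05) − μ(25,0)
- μ(10,.05) − μ(0,.08) and μ(25,.05) − μ(0,.08)

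Each has weight 0 on μ(0,0), so every linear combination of them does too. Any contrast against placebo has weight −1 on μ(0,0), and the interaction contrast μ(d,.05) − μ(d,0) − μ(0,.05) + μ(0,0) has weight +1. None of these can be recovered from the six. (The six have rank 5: the first minus the second equals the fifth minus the sixth.)

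**2. What a positive planned comparison implies.** Let the single effects be c and a, and the interaction i. Co-use minus alcohol is c + i; co-use minus cannabis is a + i. Both are positive whenever i > −min(a, c), a range that covers sub-additive, additive and synergistic effects.

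Illustration by simulation. Assumptions: n = 32, a = c = 0.7 SD of a paired difference, unadjusted two-sided 0.05, 5,000 runs.

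| True interaction | Two planned contrasts reject | Interaction test rejects |
|---|---|---|
| −0.2 | 78% and 79% | 13% |
| 0 | 97% and 97% | 4.7% |
| +0.5 | 100% and 100% | 50% |

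**3. The mixed model, main effects only.** There are 1 + 2 + 2 = 5 condition parameters, all identified by the seven cells. But i = 0 is assumed, so additivity cannot be tested. If it is false, the estimates shift. Let i₁₀ and i₂₅ be the interactions at 0.05%. Least squares on the complete 2 × 3 part fits μ(0,0) as alcohol-0% mean + cannabis-0 mg mean − grand mean. Counting only the interaction terms, this is 0 + 0 − (i₁₀ + i₂₅)/6. The 0.08% cell has its own parameter and is fitted exactly. Hence:

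- estimated 0.08% effect = true effect + (i₁₀ + i₂₅)/6
- estimated 0.05% effect = true effect alone + (i₁₀ + i₂₅)/3
- estimated effect of dose d = true effect alone + i_d/2

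**4. The mixed model, full factorial.** Parameters: 1 + 2 + 2 + (2 × 2) = 9. Cells observed: 7. The product columns 0.08% × 10 mg and 0.08% × 25 mg are zero in every observed row, so the rank is 7.

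| Quantity | Estimable? |
|---|---|
| Marginal 0.05% against 0% | yes |
| Marginal 0.08% against 0% | no |
| Marginal 10 mg or 25 mg against 0 mg | no |
| Interaction 0.05% × 10 mg, 0.05% × 25 mg | yes |
| Interaction 0.08% × 10 mg, 0.08% × 25 mg | no |

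Marginal means for 0.08%, 10 mg and 25 mg each average over a cell that was never run, so omnibus tests depend on how the software treats empty cells.

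**5. What the sessions can support.** As contrasts of cell means, 10 mg, 25 mg, 0.05% and 0.08% against 0/0 are all estimable, and so are both 0.05% interaction contrasts.

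**The case against.** The strongest reply is that the mixed model is the general analysis and has 0% and 0 mg as explicit levels. A reader might infer that the placebo session goes unused, or that the trial cannot detect its own positive control. The documents do not support either: the session is in the model, and 0.08% against 0/0 is estimable as a cell contrast. What stands is that no such contrast is named and that the stated factors do not deliver it cleanly.

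Second, the rank deficiency and the missing interaction test cannot both be charged at once. If interactions are fitted, the two useful ones are available; if they are not, there is no deficiency. That is right, and they are alternatives. An article may also leave model terms to a fuller plan. But each reading falls short in its own way (steps 3 and 4), and the article itself fixes both the factor levels and the comparison list.

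Third, section 3 pairs the words additive and synergistic and ties them to the 0.08% benchmark, which is a planned comparison. A reader might infer a formal hypothesis of synergy against additivity; none is stated. Still, exceeding a benchmark says nothing about additivity, and the listed comparisons do not exclude sub-additive effects.

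The planned comparisons themselves use observed cells and are unaffected by the empty ones.

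**Conclusion.** The point holds for the analysis as specified, not for the design. None of the six planned contrasts uses the placebo/placebo session and none tests an interaction. The model factors imply nine cells where seven exist, and neither natural reading of the model fills the gap. As written, the comparisons support statements that co-use is worse than one drug, or differs from 0.08% alcohol. They do not support effects alone against placebo, a confirmed positive control, or the description additive or synergistic.

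Steps 1 and 4, and the inequality in step 2, rest on no numerical assumption. The shifts in step 3 assume complete data. The simulation rates depend on the assumed 0.7 SD effects and are illustrative only.

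Two further readings should be resisted. It is tempting to say the trial has only about 51% power for an interaction. That figure assumes pairwise power of exactly 80%, an interaction of the same raw size and compound symmetry, while the article states 0.80 only as a floor. It is also tempting to require that 0.08% against placebo be tested first as a gate. That is one possible design preference, and the point does not need it.

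**What to change.** 1. Model condition as one 7-level within-subject factor, alongside time and sex. Equivalently, use a 2 × 3 factorial (0% and 0.05% by 0, 10 and 25 mg) with 0.08% as a separate cell.
2. Add planned contrasts of 10 mg, 25 mg, 0.05% and 0.08%, each against placebo/placebo.
3. Add the two interaction contrasts, [dose + 0.05%] − [dose] − [0.05%] + [placebo], for 10 mg and 25 mg.
4. Put the enlarged set, 6 + 4 + 2 = 12 contrasts per outcome, within the stated Holm procedure.
5. Report the interaction estimates with confidence intervals. Claim synergy only if the interval excludes zero in the direction of greater impairment. An interval that includes zero does not show additivity; in that case drop the wording additive or synergistic. Since section 2.14 allows data transformations, state the scale on which additivity is judged.

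Cost: plan wording only, with no change to sessions, sample size or data collection. The downsides are more contrasts in the multiplicity family and less precise interaction estimates. A four-cell contrast has variance 4σ² against 2σ² for a pairwise one under assumed compound symmetry (σ² the within-subject variance), so its standard error is √2 times as large.
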